#### Primary endpoint measure

MBIn [25, 26]) emotional exhaustion subscale, which represents the primary endpoint.

#### Secondary endpoint measures

MBIn depersonalization and professional achievement subscales,Hospital Anxiety and Depression Scale (HADS [31, 32]),*Perceived Stress Scale* (PSS [33, 34]),Difficulties in Emotional Regulation Scale (DERS [35, 36]),Fagerstrom Test for Cigarette Dependence (FTCD [37, 38]),Alcohol Use Disorders Identification Test (AUDIT [39, 40]),Drug Abuse Screening Test (DAST [41, 42]),Cannabis Abuse Screening Test (CAST [43]),Jefferson Scale of Empathy, student version (JSEs [44, 45]),Five Facet Mindfulness Questionnaire (FFMQ [46, 47]),Self-Compassion Scale (SCS [48, 49]),World Health Organization Quality of Life (WHOQOL-BREF [50, 51]),Numerical scales (from 0 to 10) for current and worst (during the last 15 days) psychological and physical pain, and for suicidal ideation.

The acceptability of the two interventions will be assessed through the number of missed sessions, and satisfaction using a Likert scale from 0 (not useful at all) to 10 (extremely useful). Table 1 summarizes the assessments performed at each visit.

**Table 1 Tab1:** Assessments at the different time points

Instrument	Target	Visit 1 Inclusion	Visit 2 Within the 1st month post-intervention	Visit 3 6 months post-intervention	Visit 4 12 months post-intervention
MINI 7	Lifetime psychiatric disorders	X			
MADRS	Depression	X	X	X	X
C-SSRS	Suicidality	X	X	X	X
MBIn	Emotional exhaustion, Depersonalization & Professional achievement	X	X	X	X
Fagerstrom	Tobacco use	X			X
AUDIT	Alcohol use	X			X
DAST	Illicit substances use	X			X
CAST	Cannabis use	X			X
HADS	Anxiety-depressive symptomatology	X	X	X	X
PSS	Perceived stress	X	X	X	X
Numerical scales	Psychological pain Physical pain Suicidal ideation	X	X	X	X
Numerical scale	Intervention satisfaction		X		
JSEs	Empathy	X	X	X	X
DERS	Emotional regulation	X	X	X	X
IRI	Interpersonal reactivity	X			X
WHOQoL-BREF	Quality of life	X			X
FFMQ	Mindfulness skills	X	X		X
SCS	Self-compassion	X	X		X

*MINI 7* International Neuropsychiatric Interview, *MADRS* Montgomery Asberg Depression Scale, *C-SSRS* Columbia Suicide Severity Rating scale, *MBIn* Maslach Burnout Inventory, *AUDIT* Alcohol Use Disorders Identification Test, *DAST* Drug Abuse Screening Test, *CAST* Cannabis Abuse Screening Test, *HADS* Hospital Anxiety and Depression Scale, *PSS* Perceived Stress Scale, *JSE* Jefferson scale of empathy student version, *DERS* Difficulties in Emotional Regulation Scale, *IRI* Interpersonal reactivity index, *WHOOQL-BREF* World Health Organization Quality of Life, *FFMQ* Five Facet Mindfulness Questionnaire, *SCS* Self-compassion scale

### Statistical analyses

Demographic data and baseline characteristics will be presented for the whole population and for each intervention group. Categorical variables will be described as numbers and percentages, and quantitative variables as mean and standard deviation or median and range, according to their distribution (normal or not).

The MBIn emotional exhaustion subscale score (primary endpoint) will be compared in the two groups at the end of the trial. An analysis of covariance will be performed including the baseline emotional exhaustion subscale score and baseline covariates that are found to be significantly different in between-group comparisons. If the conditions for carrying out a covariance analysis are not met, the continuous variable will be dichotomized and logistic regression models will be implemented.

The same methodology will be used to analyze the secondary endpoints at visit 4.

Mixed models will be used to study variations (intra- and between-group) of each variable during the follow-up. All statistical analyses will be performed using SAS® (SAS Institute, Cary, NC, USA) and the significance level will be set at *p* < 0.05.

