**Methods:**

This multicenter randomized controlled trial (“Must prevent”) plans to enroll 612 students in the fourth and fifth year of medical studies from nine French universities. After inclusion, they will be assigned randomly to the MBI or RT group. Both interventions are structured around an 8-week program that includes one group class per week and daily at-home exercises. The primary endpoint is the emotional exhaustion score assessed with the Maslach Burnout Inventory at month 12 of the follow-up. Secondary endpoints include anxiety-depressive symptomatology, suicidality, psychoactive substance use, depersonalization, psychological and physical pain, empathy, emotional regulation, self-compassion, mindfulness, quality of life, and program acceptability. Evaluations will be done before and immediately after the 8-week intervention, and at month 6 and 12 of the post-intervention follow-up.

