### Sample size

The sample size calculation was based on the results of the work by Verweij et al. [24]. In this randomized controlled trial, the mean baseline score of the emotional exhaustion subscale of the Maslach Burnout Inventory (MBIn) [25]. of 148 residents working in one of the medical, surgical or primary care disciplines was 15.6 (SD = 7.5). Assuming that the baseline score distribution will remain unchanged at the end of the trial in the MBI group, 274 students per group are required to show a significant mean between-group difference of 1.8 points for the emotional exhaustion subscale score at the end of the trial (15.6 for the MBI group and 17.4 for the RI group) with a statistic power of 80% and a 2-sided α level of 0.05. The percentage of participants lost to follow-up is estimated at 10%. Therefore, in total 612 students need to be recruited in the nine universities participating in the trial.

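### As described, the primary month-12 ANCOVA makes no use of the post-intervention and month-6 exhaustion scores, so loss that depends on those scores and differs between arms could bias it; the mixed model already planned would guard against this.

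*Protocol article*

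**What the plan says.** The abstract fixes the endpoint and time point: "The primary endpoint is the emotional exhaustion score assessed with the Maslach Burnout Inventory at month 12 of the follow-up". The Statistical analyses section gives the comparison, "The MBIn emotional exhaustion subscale score (primary endpoint) will be compared in the two groups at the end of the trial", and the model: "An analysis of covariance will be performed including the baseline emotional exhaustion subscale score and baseline covariates", the covariates being those that differ significantly between groups at baseline. The same approach is to be used for the secondary endpoints at visit 4.

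A separate sentence of that section adds "Mixed models will be used to study variations (intra- and between-group) of each variable during the follow-up". It does not link these models to the primary comparison.

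The abstract also states "Evaluations will be done before and immediately after the 8-week intervention, and at month 6 and 12 of the post-intervention follow-up", and Table 1 shows the Maslach inventory at all four visits. The Sample size section says "274 students per group are required to show a significant mean between-group difference of 1.8 points", and "The percentage of participants lost to follow-up is estimated at 10" per cent, which leads to 612 recruited.

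The article names no analysis set and no method for missing month-12 scores.

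**The concern.** An ANCOVA of a single end-of-trial score needs one outcome value per student. Used as described, it has no place for a student who gave scores at visits 2 and 3 but missed visit 4. Those interim scores are the best available information on what the missing value would have been.

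Loss related to exhaustion is plausible here. Each arm asks for eight weekly sessions of 150 minutes plus up to 45 minutes of daily home practice, with follow-up to month 12. The Discussion itself notes how little time medical students have and that wellness activities can feel like one more duty. If the more exhausted students leave one arm more often than the other, the visit 4 completers are no longer comparable, and baseline adjustment repairs this only in part. The target difference is 1.8 points, or 1.8/7.5 = 0.24 SD, so shifts of a few tenths of a point matter. The error can hide an effect or exaggerate one.

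**Working it through.** **1. The plan's own figures.** Inputs from the Sample size section: means of "15.6 for the MBI group and 17.4 for the RI group" (difference 1.8), SD 7.5, power 80%, two-sided 5%.

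- Normal approximation: n = 2 × (1.960 + 0.842)² × 7.5² / 1.8² = 273 per group. The t-test version gives 273.5, so 274. Reproduced.
- 10% loss: 274/0.9 = 305 per group, 610 in total; or 548/0.9 = 609. The stated 612 (306 per group) agrees closely.
- 306 × 0.9 = 275 per group remain, with power 80.4% before baseline adjustment. Planned power survives the planned loss, so the issue is bias.

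**2. Assumptions for the bias.** The documents give only the overall 10% loss. The following are assumed: SD 7.5 at every visit; correlation 0.5 between baseline and each later visit; correlation 0.65 between visits 3 and 4; loss occurring after visit 3, with odds multiplied by 2.5 per SD of the visit 3 score (log odds ratio β = ln 2.5 = 0.916).

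**3. Approximate formula.** If a proportion p is lost with log odds ratio β per SD, the mean visit 3 score of those remaining shifts by about −βp SD. After adjustment for baseline, the part carried into visit 4 is r34 − r03 × r04 = 0.65 − 0.5 × 0.5 = 0.40. Hence

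bias in (RT − MBI) ≈ −7.5 × 0.40 × (β_RT p_RT − β_MBI p_MBI).

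With |β| = 0.916 in both arms, 7.5 × 0.40 × 0.916 = 2.75.

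| Loss pattern | Formula | Simulated completer ANCOVA | Simulated, using visits 2–3 |
|---|---|---|---|
| 10%/10%, same relation in both arms | 0 | 1.80 | 1.80 |
| MBI 8%, RT 12%, same relation | −2.75 × 0.04 = −0.11 | 1.70 | 1.80 |
| MBI 5%, RT 15%, same relation | −2.75 × 0.10 = −0.28 | 1.57 | 1.82 |
| 10%/10%, opposite relations (high scorers leave RT, low scorers leave MBI) | −2.75 × 0.20 = −0.55 | 1.27 | 1.78 |

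The true difference is 1.80. The simulated values come from large samples, so their error is a few hundredths. Reversing the arms reverses the sign: 15% MBI and 5% RT gives 2.06 against 1.80.

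**4. Sensitivity to the assumptions.** With one common correlation of 0.5 to 0.7 between all visits and 10% loss in each arm, completer ANCOVA is off by −0.13 to −0.16 when loss is score-related in one arm only, and by 0.24 to 0.35 when the relations are opposite. At 30% loss these become −0.37 to −0.47 and 0.79 to 0.91. The estimate using visits 2 and 3 stays between 1.75 and 1.84 throughout.

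**5. Scale.** With 275 per group and r = 0.5, the standard error of the ANCOVA estimate is about 7.5 × √(1 − 0.25) × √(2/275) = 0.55. A bias of 0.25 is a little under half of that. When loss is unrelated to the scores, using visits 2 and 3 cuts the variance by only about 3%.

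**The case against.** The strongest reply is that the article never says the analysis is limited to students with a visit 4 score. An ANCOVA can be run after multiple imputation from visits 2 and 3, which would give much the same protection, and imputation is normally set out in a full protocol or SAP that is not at hand. This stands, and it is why the point is conditional. A reader might infer that students lost to follow-up are simply deleted, and might take the step from 274 per group to 612 as proof. The documents do not support that: enlarging the sample for expected loss is routine whatever method handles missing data. It shows how the number was set, not how the data will be analysed.

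It is also too strong to say that completer ANCOVA is unbiased only if loss depends on nothing beyond arm and baseline. The first row of the table shows essentially no bias when loss depends on the visit 3 score alike in both arms.

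Nothing in the documents points to unequal loss. The arms are matched on session length, duration and home practice, and students in both are compensated for visits 2 to 4, so similar attrition is at least as plausible. The bias figures are therefore scenarios, not forecasts.

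Finally, a baseline-adjusted ANCOVA at one prespecified time is a standard primary analysis, and the longitudinal model is already in the plan as support. That is so, but it does not settle which should be primary. Of two analyses that the sponsor will run anyway, the plan gives the primary role to the one with the stronger requirement on missing data.

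**Conclusion.** The point holds in conditional form. The primary model, as stated, uses no interim exhaustion score although the scores and a suitable model are already in the plan. Unless missing month-12 values are dealt with elsewhere, it rests on students with a visit 4 score.

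Under the assumed correlations and odds ratio, the resulting bias is about 0.1 points (0.1/1.8 = 6% of the target) at 8%/12% loss, about 0.25 points (14%) at 5%/15%, and up to about 0.5 points (28%) with opposite mechanisms. It is about zero if loss works alike in both arms. If loss depends on the month-12 score itself, which is unobserved, neither analysis is protected.

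This is a change worth making because it costs little. It does not make the planned analysis invalid, and it has no bearing on the sample size, which reproduces.

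**What to change.** Name as the primary estimate the month-12 MBI–RT contrast from one mixed model of the emotional exhaustion scores at visits 2 to 4, with arm, visit, arm × visit, baseline score × visit and centre, and an unstructured within-student covariance. Include all randomised students with any post-baseline score. Keep the visit 4 ANCOVA as a sensitivity analysis.

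Do the same for secondary scores that Table 1 collects at more than one post-baseline visit, such as HADS, PSS, DERS, the empathy scale, and (visits 2 and 4 only) FFMQ and SCS. For scales collected only at visits 1 and 4, such as AUDIT or WHOQOL-BREF, there are no interim scores of the same scale to use, and ANCOVA can stay.

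The change alters no visit, no data collection and not the 612. Recruitment was still under way when the article was submitted, so at that stage it could be made before outcome data were analysed. The costs are slightly more modelling work and reliance on a missing-at-random assumption. Students with no post-baseline score still contribute nothing.

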### Procedure

Recruitment will take place in nine French medical universities (Montpellier, Paris, Marseille, Nîmes, Strasbourg, Clermont-Ferrand, St Etienne, Angers and Tours) where the study will be advertised and students will receive general information. Students interested in participating will be included after verification of their eligibility and after signing an informed consent form obtained via the investigators. Participants will be randomized to the MBI or the RT group by an independent researcher, not otherwise involved in the study. Randomization will be stratified by study center and degree of emotional exhaustion (MBIn emotional exhaustion subscale score < 17, 18–29, and ≥ 30 [25, 26]). Randomization will be centralized, accessible online and programmed using the Capture Software System (EnnovClinical randomization module) according to a minimization algorithm with a 1:1 ratio.

Participants not included in the study because of a current depressive episode or panic disorder will be referred to the psychological unit of their university.

Participants will be evaluated at four time points (Fig. 1): before (i.e. within 6 weeks) the intervention (visit 1), within the month after the intervention end (visit 2), and at month 6 (visit 3) and month 12 (±1 month; visit 4) of the post-intervention follow-up. Raters will be blind to the allocation (simple-blind). Research assistants and MBI/RT instructors will emphasize the importance of blinding to participants and will repeatedly remind them not to reveal their intervention type. In case of unblinding, another assessor will repeat the entire measurement.

A monetary compensation (40 euros) will be given to participants after each follow-up visit (visits 2 to 4) for the time devoted to the study.

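### The primary ANCOVA picks covariates by baseline significance tests and does not name centre, a minimisation factor; the result is an unfixed and, if centre is prognostic, mildly conservative analysis

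*Protocol article*

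**What the plan says.** The Statistical analyses section of the protocol article sets out the primary model: "An analysis of covariance will be performed including the baseline emotional exhaustion subscale score", together with "baseline covariates that are found to be significantly different in between-group comparisons". The article gives no list of candidate covariates. The only significance level stated is the general 0.05. The same method is then applied to the secondary endpoints at visit 4, and mixed models are planned for changes over follow-up.

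The Procedure section describes the allocation: "Randomization will be stratified by study center and degree of emotional exhaustion", carried out "according to a minimization algorithm with a 1:1 ratio". On the number of sites it says: "Recruitment will take place in nine French medical universities". The emotional exhaustion factor reaches the model through the continuous baseline score. Centre is not mentioned in the model.

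**The concern.** There are two connected problems.

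First, if allocation is properly randomised, any significant baseline difference is a chance finding. Testing for such differences says nothing about whether a variable predicts emotional exhaustion at month 12, which is the reason to adjust for it. A strong predictor that happens to be balanced stays out, and an irrelevant variable that happens to be unbalanced goes in. The primary model is also settled only after the arms have been compared at baseline, and the rule carries over to every secondary endpoint at visit 4.

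Second, minimisation keeps the arms alike on centre, so a test of centre by arm will almost never be significant and the rule will almost never admit it. Balancing on a prognostic factor reduces the true variance of the treatment estimate. A model without that factor does not see the reduction and reports too large a standard error. An effect of centre is plausible here because the MBI and RI programs section assigns two instructors to each centre.

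At stake are a primary analysis that is not fixed in advance, intervals somewhat wider than they need be, and some precision given up in a trial that looks for a small difference (1.8 points on an SD of 7.5, or 0.24 SD).

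**Working it through.** **Reproducing the plan's own figure.** The inputs from the Sample size section are a difference of 1.8, SD 7.5, 80% power, two-sided 0.05 and 10% loss.

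- Normal approximation: n = 2 × (1.960 + 0.842)² × 7.5² / 1.8² ≈ 272.5, so 273 per arm.
- The t-test solution is 273.5, so 274 per arm, as stated. Power at 274 is 0.802.
- Loss: 274 / 0.9 = 304.4, so 305 per arm and 610 in total, close to the stated 612.

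This calculation uses the unadjusted SD, which matters for the conclusion on power.

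**Chance selection.** With K independent candidates each tested at 0.05, the expected number selected is 0.05K and P(at least one) = 1 − 0.95^K. K is an assumption, because the article gives no candidate list.

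| K | Expected number | P(at least one) |
|---|---|---|
| 10 | 0.5 | 40% |
| 15 | 0.75 | 54% |
| 20 | 1.0 | 64% |
| 25 | 1.25 | 72% |

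The expected number holds whatever the correlation. The probability of at least one falls when the candidates are correlated, as several of the listed mood and stress scales probably are.

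**Leaving out centre.** Assumptions: correlation r = 0.5 between baseline and month-12 score, centre explaining a share s of outcome variance, exact balance on centre, and 274 analysed per arm.

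- Standard error reported without centre: 7.5 × √0.75 × √(2/274) = 0.555.
- True standard error: 7.5 × √(0.75 − s) × √(2/274).
- Ratio: R = √(0.75 / (0.75 − s)).
- Type I error = 2 × [1 − Φ(1.96R)]; coverage is its complement.
- Power without centre = Φ[(1.8 − 1.96 × 0.555) / true SE]; with centre = Φ[1.8 / true SE − 1.96].

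| s | R | Type I error | Coverage | Power without centre | Power with centre |
|---|---|---|---|---|---|
| 1% | 1.007 | 0.0485 | 95.2% | 0.902 | 0.904 |
| 2% | 1.014 | 0.0470 | 95.3% | 0.903 | 0.908 |
| 5% | 1.035 | 0.0425 | 95.8% | 0.908 | 0.919 |
| 10% | 1.074 | 0.0353 | 96.5% | 0.916 | 0.936 |

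In the row s = 5%, for example, the true standard error is 0.536, so 1.8 / 0.536 − 1.96 ≈ 1.40 and power is 0.919.

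Sensitivity to r: as r goes from 0 to 0.6, the type I error runs from 0.0443 to 0.0412 at s = 5%, and from 0.0388 to 0.0329 at s = 10%.

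**The whole rule by simulation.** There were 3,000 runs with 548 analysed, nine centres, minimisation on centre and emotional exhaustion category, r = 0.5 and 20 candidates.

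- No prognostic value in centre or covariates: type I error 0.0497, which is nominal.
- Five candidates prognostic (3 to 6% of variance each) and centre at 2 to 5%: type I error 0.041 to 0.032, coverage 95.9% to 96.8%, power 0.912 to 0.926.

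The simulation standard error of a 5% rejection rate is √(0.05 × 0.95 / 3000) ≈ 0.004, so only the larger departures are clear of noise.

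**The case against.** The strongest case on the other side has four parts.

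**Size of the harm.** The rule selects on baseline data and not on the outcome, and every calculation gives a type I error at or below 5%. A reader might infer from the words chance selection that false positives are inflated; nothing in the documents supports that for the rule as written. A reader might also infer that the trial is underpowered. It is not: 274 per group already gives 80% on the unadjusted SD, and adjusting for baseline emotional exhaustion can be expected to raise power. This stands.

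**Size of the gain.** In the simulation, a model that also fixes the five prognostic covariates reaches power of 0.958 to 0.993. It is tempting to credit that gain to prespecification in general. Those covariates are hypothetical, and the article identifies no variable as prognostic for month-12 emotional exhaustion. The gain that can be attributed to adding centre is about 0.2 to 2 points. Year of study is an eligibility condition, not an allocation factor, so nothing in the article requires it in the model. This stands too.

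**Assumptions.** The number of candidates, the baseline correlation and the variance share of centre are all undocumented, and the 64% needs independent tests. This is correct, and ranges are given for that reason.

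**Silence about centre.** The article is condensed and does not exclude centre, so an analysis plan might add it. That weakens the point about centre taken alone. It does not rescue the selection rule, which the article states outright. An analysis plan with a fixed covariate set would have to depart from it.

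**Conclusion.** The point holds as a rule fixed badly, not as a detail left out. Choosing covariates by baseline significance selects on chance imbalance and leaves the primary model open until the arms are compared. Centre, on which allocation is minimised, is not named and would almost never enter by that route.

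The consequence is modest and conservative. With centre at 1 to 10% of outcome variance and a baseline correlation of 0.5, the test runs at about 4.9% to 3.5% instead of 5%, with intervals slightly too wide. At a share of 2% or less the departure is negligible, and it vanishes if neither centre nor the covariates are prognostic. This should be corrected, but it does not threaten the validity of a positive result or the sample size.

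**What to change.** In Statistical analyses, delete "baseline covariates that are found to be significantly different in between-group comparisons" and drop between-group baseline tests as a means of choosing covariates. Prespecify the primary ANCOVA with treatment arm, continuous baseline emotional exhaustion and centre. Add further covariates only if they are named in advance on prognostic grounds; year of study is optional.

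For each secondary endpoint at visit 4, adjust for that endpoint's own baseline value and for centre. Carrying the primary covariate set over unchanged would adjust the other scales for baseline emotional exhaustion instead. Include centre in the mixed models. If an analysis plan already names centre, confirm this and align the wording.

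The cost is a change of text. Centre and the baseline scores are already recorded, and no new data or change in sample size is needed.

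### If ANCOVA conditions fail, the primary score is dichotomised and analysed by logistic regression: this drops the mean difference the trial is sized for and loses power

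*Protocol article*

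**What the plan says.** Protocol article, Statistical analyses: the month-12 exhaustion score is compared between groups by ANCOVA, adjusted for the baseline score and for baseline covariates found to differ between groups. If the conditions for ANCOVA are not met, "the continuous variable will be dichotomized and logistic regression models will be implemented". The section names no condition, no way of checking it and no cut. It applies the same approach to the secondary endpoints at visit 4, and adds mixed models for change in each variable over follow-up.

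Protocol article, Sample size: the size rests on means alone. The source trial's baseline score "was 15.6 (SD = 7.5"), the assumed final means are "15.6 for the MBI group and 17.4 for the RI group", and "274 students per group are required to show a significant mean between-group difference of 1.8 points" "with a statistic power of 80% and a 2-sided α level of 0.05". No power is given for a binary outcome.

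Protocol article, Procedure: randomisation is stratified by exhaustion score (below 17, 18 to 29, 30 or more). These are the only cut-points in the article, and they are not tied to the analysis.

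**The concern.** The fallback changes the primary question. The objective and the sample size concern a difference in mean score. The fallback would report an odds ratio for exceeding a threshold, and that ratio depends on which threshold is used. A score split in two also carries less information, so the trial would be underpowered for the analysis that it reports.

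Assumptions about the month-12 score can be examined only on month-12 data. The choice between two primary tests with different effect measures would therefore depend on the outcomes. With the conditions undefined in this document, that choice is open to judgement.

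**Working it through.** **Inputs.** From Sample size: means 15.6 and 17.4, SD 7.5, 274 per group, two-sided α 0.05, power 80%. From Procedure: 1:1 allocation and the stratum limits. Assumed here: normal scores and SD 7.5 in both arms. The article carries the baseline distribution forward for the mindfulness arm only ("Assuming that the baseline score distribution will remain unchanged at the end of the trial in the MBI group").

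**1. The plan's own figure.** The standard error of the difference is 7.5 × √(2/274) = 0.641, and 1.8/0.641 = 2.81. Power = Φ(2.81 − 1.96) = 80.2%. The exact two-sample t-test needs 274 per group (power 80.1%), so the stated size is reproduced. With 10% loss, 274/0.9 gives 305 per group, or 610, close to the stated 612.

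**2. Power after dichotomising.** The share above cut c is p = 1 − Φ((c − mean)/7.5). With pooled p̄ = (p₁ + p₂)/2, se₀ = √(2p̄(1 − p̄)/274) and se₁ = √((p₁(1 − p₁) + p₂(1 − p₂))/274), power = Φ((p₂ − p₁ − 1.96·se₀)/se₁).

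- Score 18 or more (c = 17.5): p₁ = 1 − Φ(0.253) = 40.0% and p₂ = 1 − Φ(0.013) = 49.5%. se₀ = 0.0425 and se₁ = 0.0423. Power = Φ((0.0947 − 0.0833)/0.0423) = Φ(0.27) = 61%.
- Score 17 or more (c = 16.5): 45.2% v 54.8%, power 61%. This cut lies midway between the two means, and it does no better.
- Score 30 or more (c = 29.5): 3.2% v 5.3%. se₀ = 0.0173 and se₁ = 0.0172. Power = Φ((0.0214 − 0.0338)/0.0172) = Φ(−0.72) = 24%. Without the half-point continuity step (c = 30) it is 22%.

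**3. Loss as sample size.** Restoring 80% power would take about 430 per group for a cut near 17, and about 1,400 for 30 or more. The central cut keeps 274/430 = 64% of the information and so loses about a third. The extreme cut keeps 274/1,396 = 20%.

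**4. Change of effect measure.** The same 1.8-point shift is an odds ratio of (0.495/0.505)/(0.400/0.600) = 1.47 at 18 or more, and (0.0533/0.9467)/(0.0319/0.9681) = 1.71 at 30 or more. Neither is the quantity in the sample size section.

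**5. With baseline adjustment** (simulation, 400 trials per setting, baseline–outcome correlation assumed). At correlation 0.5, ANCOVA has 89–90% power. Adjusted logistic regression has 69–72% for a central cut and 24% for 30 or more. Across correlations 0 to 0.7, logistic power is 61–78% (central) and 18–24% (30 or more), below ANCOVA on the same data every time.

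**6. If the check were a residual normality test.** Scores were simulated as gamma-shaped and rounded to integers, with mean 15.6, SD 7.5, assumed correlation 0.5 and 274 per arm. The Shapiro–Wilk test on residuals rejected in all 400 trials tested. ANCOVA type I error was 4.9% and power 89% (4,000 trials each). A second, similar simulation (2,000 trials) gave 5.4%, 90% and 100% rejection.

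**The case against.** **An unseen analysis plan may fix the cut and define the conditions.** This is fair: an article commonly leaves such detail out. A reader might infer that the cut will be picked after looking at the data. The article does not say so; only the decision to switch has to wait for outcomes. Under no effect, free choice of the smallest p-value among the mean comparison and two cuts (near 17 and at 30) would give about 12% false positives instead of 5% (20,000 simulations). That is an upper bound on a practice the article does not describe. A cut fixed in advance would remove this worry, but not the change of effect measure or the loss of power.

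**The power figures are illustrative.** They assume normal scores with equal SD, the situation in which a normality or variance check should not fail. Under gamma-shaped scores, power is about 55–66% for cuts at 16.5 to 17.5. At 29.5 it is 14–39%, depending on how the effect enters. The direction holds; 24% is not a stable figure.

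**The conditions need not mean normality.** Unequal slopes, non-linearity or unequal variances are equally possible readings, and step 6 says nothing about them. A reader might conclude that the switch would always fire needlessly; that is supported only for a normality test.

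**The mixed models also cover the exhaustion score.** True, but they are not the primary test.

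**Dichotomising can suit some secondary scores.** This stands: substance-use scales and the 0–10 suicidal-ideation scale may have many zeros (an assumption), and the calculations here concern the exhaustion score only.

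**Conclusion.** The point holds for the primary endpoint. The main analysis, a baseline-adjusted ANCOVA, matches the objective and the sample size; the contingent clause does not. It is a stated rule rather than an omission, so an analysis plan could add a cut without curing it.

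On the article's own means and SD, with the normality and equal-SD assumptions above, power drops from 80% to about 61% for a central cut. The 24% at 30 or more shows how bad an extreme cut could be and is not a forecast, since nothing in the article points to that cut. It would overstate the case to say that most of the information is lost or that the planned power is destroyed: for a central cut the loss is about a third. If the check is a residual normality test, a moderately skewed score would trigger the switch although ANCOVA remains valid at this sample size.

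**What to change.** For the primary endpoint, delete the dichotomise-and-logistic fallback. Keep the baseline-adjusted difference in mean score as the primary estimate in all cases. If residuals are non-normal or variances unequal, use heteroscedasticity-robust standard errors or a bootstrap confidence interval for that same difference, with a rank-based analysis as sensitivity.

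If a threshold result is wanted, report it as a secondary, supportive analysis at a cut fixed before outcome data are seen. Secondary scores with many zeros may be given their own method.

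The cost is a sentence or two in Statistical analyses, with no extra participants and no design change. Recruitment was still under way when the article was submitted and the endpoint is at month 12, so the change could be made before the primary outcome is analysed.
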